   1. GCP

The study will be conducted in accordance with principles enunciated in the current Declaration of Helsinki („59th WMA General Assembly“, Seoul, October 2008), the guidelines of Good Clinical Practice (GCP) issued by ICH, and Swiss regulatory authority’s requirements. The Principal Investigator will require a copy of the Ethic’s approval letter before accepting participants into the study.

- - 1. Criteria for premature termination of the trial

The Principle Investigator reserves the right to discontinue the trial at any time. In terminating the trial, the investigator will assure that adequate consideration is given to the protection of the interests of all subjects. The Principle Investigator must notify the Ethics Committee of the premature termination.

- - 1. Publication policy

The results of this study will be presented as scientific papers in an adequate journal. This trial will be registered in a public clinical trial database (anticipated: SNCTP and ICTRP).

- 1. Reporting Procedures

All adverse events will be reported. Depending on the nature of the event the reporting procedures below should be followed. Any questions concerning adverse event reporting will be directed to the Principal Investigator in the first instance. The Principle Investigator will report severe adverse reactions, changes (to the protocol), intermediate and final reports to the ethic commission.

- - 1. Definitions

**AE**

An Adverse Event (AE) is any untoward medical occurrence in a patient or clinical investigation subject administered a study product and which does not necessarily have a causal relationship with this treatment (ICH-GCP definition).

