| Statistical Methodology: | Acquired H_2_-measurements and metabolic profiles will be analyzed according to standard algorithms. Several algorithms are available (see below). Microbial gut communities will be analyzed by 16S rRNA sequencing and compared using hpc-clust (see below). |
| Statement: | This study will be conducted in compliance with the protocol, the current version of the Declaration of Helsinki („59th WMA General Assembly“, Seoul, October 2008), and ICH-GCP as well as all national legal and regulatory requirements. |

- 1. Study Flow chart

Informed consent will be obtained during a separate visit. The study will be finished within 15 days for each individual, with one main study day. The following basic steps will be performed:

- Informed consent will be obtained during the first study visit. At that time,basic medical history and gastrointestinal complaints will be addressed, dates for the lactulose breath test will be agreed on

- One to three days before the lactulose or sham test the volunteer collects a fecal and a urine sample using the restrooms of his/her workplace at the Institute of Microbiology, ETH Zurich and directly snap-freeze it using liquid nitrogen. The samples will be stored by the proband at -80°C (at biosafety level 2).

- a lactulose breath test or a sham test will be carried out

- Within the next two days, the proband will collect a fecal and urine sample at his/her workplace, snap-freeze it and store it at -80°C.

- 14 days after the lactulose breath test, the volunteer will take additional fecal and urine samples following the same procedure.

- Finally, all stool and urine samples will be assembled at ETH for further processing.

- 1. List of abbreviations

AE Adverse Event

BMI Body Mass Index

CRF Case Report Form

GCP Good Clinical Practice

GI Gastrointestinal

LHT Law on human research

HMG Heilmittelgesetz

ICH International Conference on Harmonisation

IEC Independent Ethics Committee

ClinO Clinical Trial Ordinance

i.g. Intragastric

h hour

g gramm

Art.nr article number

BL2 Biosafety Level 2

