6.2. Parameters for assessing protocol compliance

Parameters for assessing protocol compliance in this study are (checked by study nurse):

- Refrain from substances that might alter gut microbiota (including proton pump inhibitors, laxatives and antibiotics) unless medically necessary

- Collection of the required samples (3 fecal samples, 3 urine samples)

- Completion of measurement of hydrogen content of exhaled air after lactulose intake (lactulose breath test).

1. SAFETY of conducted procedures
   1. Fecal and urine sample collection

Volunteers will be provided with individually numbered cryotubes and will be asked to collect fecal and urine samples using the restrooms at the Institute of Microbiology, ETH Zurich. After sample collection, the proband snap-freezes the samples in liquid nitrogen and transfers the samples to a -80°C freezer (Biosafety Level 2). Liquid nitrogen and -80° freezers can be handled very safely with some basic training and compliance with few basic precautions. During recruitment we will ensure that all probands are trained in handling liquid nitrogen and 80°C freezers at biosafety level 2 (this is the case for near all scientific members at ETH). All probands will wear suitable protection (gloves and googles). As handling liquid nitrogen is part of their regular working routine, this step will not impose an additional risk to our volunteers. Furthermore, handling of stool or urine from other individual carries a small risk for infections. However, this is not the case if an individual handles his or her own stool or urine and autoinfection is not a concern.

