**SAE**

A Serious Adverse Event (SAE) is any untoward medical occurrence or effect that at any dose:

- results in death

- is life-threatening (at the time of the event)

- requires hospitalization or prolongation of existing subjects’ hospitalization

- results in persistent or significant disability or incapacity

- results in a congenital anomaly or birth defect

- - 1. (S)AE recording

Any (S)AE as reported spontaneously by the subject or observed by the investigator or staff, is recorded on the AE form during the course of the study. The investigator must ensure that this information, including onset, duration and nature of event, severity, and action taken, is captured. SAEs must additionally be recorded on the SAE report form.

The severity of any (S)AE is scored as follows:

**Mild:** transient or mild discomfort; no medical intervention/therapy required

**Moderate:** mild to moderate limitation in activity; some assistance may be needed; and/or minimal medical intervention/therapy required

**Severe:** marked limitation in activity; some assistance usually required; and/or significant medical intervention/therapy/hospitalization required

The relationship of the (S)AE to the study product is assessed as being “not related / unlikely / possibly / probably / definitely related”.

- - 1. SAE reporting by the investigator

The investigator must report the SAE to the principal investigator as soon as possible. The investigator must complete the SAE report within 48 hours (working days) after first notice. The follow-up report should be completed as soon as possible and handed over the report to the principal investigator.

- - 1. SAE review and reporting by the Sponsor

The principle investigator must review all reported SAEs. The principle investigator must report all deadly SAEs and all life threatening SAEs causally related to the study immediately (within 7 days) to the accredited Ethics Committee that approved the protocol. Other SAEs causally related to the study must be reported within 15 days. SAEs are reported annually as line listings or according to the requirements of the Ethics Committee.

- - 1. Follow-up of (S)AEs

All (S)AEs are followed-up by the investigator until they have abated, or until a stable situation has been reached. Depending on the event, follow-up may require additional tests or medical procedures as indicated, and/ or referral to the general physician or a medical specialist.

- 1. Insurance

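### The adverse event definition starts only once study product has been given, so it misses the baseline liquid-nitrogen sampling, and the only causality score does not record the study-level judgement that expedited reporting needs

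*Protocol*

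**What the plan says.** Section 10.2.1 of the protocol covers "any untoward medical occurrence in a patient or clinical investigation subject administered a study product" and adds that the event is one "which does not necessarily have a causal relationship with this treatment". An AE therefore needs prior administration of product but no causal link to it. The SAE definition that follows is worded differently: it covers "any untoward medical occurrence or effect that at any dose" meets one of the listed outcomes, and does not repeat the administration condition.

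Section 10.2.2 says that an AE or SAE "is recorded on the AE form during the course of the study", and provides one causality item: "The relationship of the (S)AE to the study product is assessed as being" one of five grades, from not related to definitely related. Section 10.2.4 sets the ethics-committee deadlines by a different criterion. There is a 7-day deadline for deadly SAEs and for study-caused life-threatening ones, and then: "Other SAEs causally related to the study must be reported within 15 days".

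On procedures, section 2.1 states: "One to three days before the lactulose or sham test the volunteer collects a fecal and a urine sample". Section 7.1 has the participant do the freezing in liquid nitrogen, with gloves and goggles, and concludes: "As handling liquid nitrogen is part of their regular working routine, this step will not impose an additional risk to our volunteers".

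**The concern.** This trial exposes participants to two things: the test drink, and a sampling procedure that they carry out themselves with liquid nitrogen. The protocol treats the second as a matter needing training, protective equipment and exclusion of anyone uncomfortable with it (4.2, 7.1, 9.5, 11.3.1). The safety definitions are written around the first only.

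Two consequences follow. A cold burn or eye injury at the baseline sample has no clear place on the AE form. At the later samples the injury is recorded, but the form asks only whether lactulose or sucrose caused it. The honest answer is that it did not, and there is nowhere to record that the study procedure did.

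At stake is the completeness of the safety record for a step said to carry no additional risk, and a documented basis for deciding whether an SAE meets the 7- or 15-day rule. Other safeguards are limited. Section 10.2.2 relies on spontaneous reports and staff observation, sampling takes place at the participant's workplace, and section 12 plans no further monitoring.

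**Working it through.** No sample-size, error-rate or event figure bears on this point, and the protocol states no figure to reproduce. The check sets the definitions against the sampling schedule.

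**Inputs**
- Sampling occasions per participant: 3 (sections 2.1, 4.2). The first is 1 to 3 days before the drink, the second within 2 days after it, the third 14 days after it.
- Samples per participant: 3 stool and 3 urine (6.2).
- Complete participants: 40 (8.4).

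**Step 1: is an injury at each sampling an AE or SAE?**

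| Sampling | Product already given? | Non-serious injury an AE under 10.2.1? | Serious injury an SAE? |
|---|---|---|---|
| Baseline | No | No, read literally | Unclear: no administration condition, but the wording refers to dose |
| Within 2 days after | Yes | Yes, whatever the cause | Yes |
| Day 14 | Yes | Yes, whatever the cause | Yes |

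The recording rule in 10.2.2 has no dose-based start, but this does not settle the first row. It tells staff to record AEs and SAEs, and the term AE is already limited by 10.2.1.

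**Step 2: does the causality score answer the reporting question?**

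| Section | Question asked | Answer for a freezing injury |
|---|---|---|
| 10.2.2 (form) | Related to the study product? | Not related |
| 10.2.4 (7- and 15-day rules) | Causally related to the study? | Yes |

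Both answers can be correct, because the questions differ. The form holds only the first, while the deadlines depend on the second. No section says how one is derived from the other.

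**Step 3: extent**
- Share of sampling occasions before product: 1 of 3.
- Samples frozen, assuming one freezing per sample: 40 × (3 + 3) = 240, of which 40 × (1 + 1) = 80 are before product and 240 − 80 = 160 after.

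These are counts of exposures, not of injuries or lost reports. The 160 later freezings lie inside the AE definition.

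**The case against.** A reader might infer that freezing injuries escape both AE recording and expedited reporting altogether. The documents do not support that, for three reasons.

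- At the two later samplings any injury is an AE, because no causal link is required. It is recorded with its nature, severity and action taken. A score of not related to the product is a correct answer and does not remove the event.
- The trigger in 10.2.4 refers to the study, not the product. On its wording it already covers sampling and freezing.
- A serious injury at baseline is not plainly excluded, since the SAE definition omits the administration condition.

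It can also be said that 10.2.4 never refers to the 10.2.2 score, that the principal investigator must review every reported SAE at this single centre, and that the AE text is labelled as the ICH-GCP definition. Section 10.3 (Insurance) separately requires emergency treatment to be reported to the investigator, with no dosing condition.

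All of this stands, and it confines the point. The idea that a site would read reportability off the product score is conjecture. Two things remain. Citing a standard product-based definition does not bring the baseline procedure inside it. The insurance clause informs the investigator but does not feed the AE form or ethics reporting, and its general duty to report health problems is worded around study treatment.

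**Conclusion.** The point holds in a narrow form and is minor. A non-serious injury at the baseline sampling, one of three occasions, is not an AE on a literal reading of 10.2.1; the status of a serious one is ambiguous. For injuries after the drink the gap is not in capture but in documentation: the form does not record the study-level causal judgement on which the 7- and 15-day rules rest.

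This rests on reading 10.2.1 as written and on the AE and SAE forms following 10.2.2; the forms themselves are not among the documents. With no injury rate given, and with trained participants doing work they do routinely, nothing here shows that any event, still less a serious one, would in fact go unreported.

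**What to change.** - **10.2.1:** count AEs and SAEs from informed consent (or from the first study procedure) to the day-14 sample, whether or not product has been given.
- **10.2.2:** keep the product rating and add a second one, for relatedness to study procedures (sampling, snap-freezing, breath test).
- **10.2.4:** keep the present study-level trigger and state that relatedness to either the product or a study procedure meets it. Do not replace it with a list of relatedness grades. That would be no broader than the present wording, and it could narrow the reporting of deaths, because the 7-day sentence can be read as covering every deadly SAE whatever its cause. No relatedness condition should be added to deaths.

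The cost is protocol wording, one extra field on the AE and SAE forms, and possibly a few more listed events. Design, sample size and analysis are unaffected.

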**SAE**

A Serious Adverse Event (SAE) is any untoward medical occurrence or effect that at any dose:

- results in death

- is life-threatening (at the time of the event)

- requires hospitalization or prolongation of existing subjects’ hospitalization

- results in persistent or significant disability or incapacity

- results in a congenital anomaly or birth defect

- - 1. (S)AE recording

Any (S)AE as reported spontaneously by the subject or observed by the investigator or staff, is recorded on the AE form during the course of the study. The investigator must ensure that this information, including onset, duration and nature of event, severity, and action taken, is captured. SAEs must additionally be recorded on the SAE report form.

The severity of any (S)AE is scored as follows:

**Mild:** transient or mild discomfort; no medical intervention/therapy required

**Moderate:** mild to moderate limitation in activity; some assistance may be needed; and/or minimal medical intervention/therapy required

**Severe:** marked limitation in activity; some assistance usually required; and/or significant medical intervention/therapy/hospitalization required

The relationship of the (S)AE to the study product is assessed as being “not related / unlikely / possibly / probably / definitely related”.

- - 1. SAE reporting by the investigator

The investigator must report the SAE to the principal investigator as soon as possible. The investigator must complete the SAE report within 48 hours (working days) after first notice. The follow-up report should be completed as soon as possible and handed over the report to the principal investigator.

- - 1. SAE review and reporting by the Sponsor

The principle investigator must review all reported SAEs. The principle investigator must report all deadly SAEs and all life threatening SAEs causally related to the study immediately (within 7 days) to the accredited Ethics Committee that approved the protocol. Other SAEs causally related to the study must be reported within 15 days. SAEs are reported annually as line listings or according to the requirements of the Ethics Committee.

- - 1. Follow-up of (S)AEs

All (S)AEs are followed-up by the investigator until they have abated, or until a stable situation has been reached. Depending on the event, follow-up may require additional tests or medical procedures as indicated, and/ or referral to the general physician or a medical specialist.

- 1. Insurance

Insurance is covered by the general liability insurance of the University hospital Zurich.

Any damage developed in relation to study participation is covered by this insurance. So as not to forfeit their insurance cover, the participants themselves must strictly follow the instructions of the study personell. Participants must not be involved in any other medical treatment without permission of the principal investigator (emergency excluded). Medical emergency treatment must be reported immediately to the investigator. The investigator must also be informed instantly, in the event of health problems or other damages during or after the course of study treatment.

The investigator will allow delegates of the insurance company to have access to the source data/documents as necessary to clarify a case of damage related to study participation. All involved parties will keep the patient data strictly confidential.

1. Ethical considerations
   1. Ethics committee

This protocol and any accompanying material provided to the subjects, such as information and informed consent sheets, are submitted to the applicable Ethics Committee by the investigator according to local legislation. Approval from the Ethics Committee must be obtained before starting the study, and should be documented in a letter to the investigator specifying the date on which the Ethics Committee met and granted the approval, the composition of the Ethics Committee, and version and date of all submitted documents. The investigator must submit a status report at least annually to the Ethics Committee that approved the protocol.

- 1. Confidentiality of study data

Data generation, transmission, archiving and analysis of personal data within this project, strictly follows Swiss legal requirements for data protection. The Principal Investigator will preserve the confidentiality of probands whose data are analyzed and is registered under the Data Protection Act. The Sponsor and the Principal investigator are responsible for the protection of personal information.

For the purpose of this study, probands data will be encrypted. Only the persons mentioned as clinical investigators and additional investigators of this study will see or receive non-anonymized data (point 1: general information). For the subsequent scientific analysis only encrypted data will be used and under no circumstances will additional researches learn about the name of the proband or other information which would make identification possible.

For encryption each proband will have a unique study number. This number will be used throughout the study for entry into an electronic form and subsequent analyses. Information facilitating identification of individual probands will not be entered. The key for encryption will be stored at the Functional Lab at USZ. Only the researchers mentioned as clinical investigators and additional investigators of the study will be able to view the key for encryption and will have the option to match the study number to an individual proband.

Encrypted proband information including the CRF and the data base will be stored at the department of microbiology at ETH Zurich. For additional protection, the data base will be password protected. The data will be stored at the servers of the ETH for at least 10 years after the publication of the last data of this analysis.

- 1. Benefits and risks assessment
     1. Safety of sample collection and storage

Probands will be asked about their confidence in handling liquid nitrogen to snap-freeze fecal and fecal samples. As all proband are employed at ETH Zurich/University of Zurich and trained and experienced in liquid nitrogen handling and -80 degree freezers (biosafety level 2), this procedure will not impose safety risks complementary to the risk exposure of a usual working routine of our proband.

- - 1. Safety of lactulose breath test

The lactulose breath test is a non-invasive diagnostic test with is routinely used at the Klinik für Hepatologie und Gastroenterologie, Unispital Zürich. The test is almost perfectly safe. Minor adverse events include discomfort, diarrhea, bloating and mild abdominal pain. Sever adverse events in healthy individuals are unknown.

- - 1. For Women

Female volunteers are not allowed to take part in the study, if a pregnancy beyond week 12 is known. The test is safe during pregnancy and for children; however, the composition of the gastrointestinal microbiota might be affected. All women will be asked about a likely pregnancy, however, since there is no risk for the woman or the unborn child, no pregnancy test will be performed.

- 1. Benefits of the current study

There will no benefit for the participants of this study. As a result of the study, the effect of lactulose intake on the gut microbiota composition will tell us, whether increased consumption of non-digestible polysaccharides might destabilize the microbial community. This in turn might increase the infection risk with enteropathogens. This benefit together with the lack of risk and only minimal inconvenience for the test subjects argue in our point of view strongly for this study.

- 1. Compensation for subjects

The study subjects will receive a financial compensation (200,- CHF) for participation in the study.

1. Quality control

The day-to-day management and coordination of the study will be coordinated through PD Dr. med. [name], [name]. med. [name], Dr. med. [name] and Dr. med. [name]. There won't be any further monitoring as there is basically no risks for the probands and only one visit in the hospital for the lactulose breath test.

- 1. Audits

The study may be subject to inspection and audit by regulatory bodies to ensure adherence to GCP, national law, and regulatory requirements.

- 1. Source data and data encryption

Source data include the medical history of the proband and questionnaires filled out by the proband before the examination (compare respective files). Source data will subsequently be transferred to the CRF. The investigators will use paper or electronic case report forms (CRF), one for each enrolled study participant, to be filled in with all relevant data pertaining to the participant during the study. All participants who either entered the study or were considered not-eligible or were eligible but not enrolled into the study additionally have to be documented on a screening log. The investigator will document the participation of each study participant on the Enrolment Log. Each subject will receive a screening number. Encoding is ensured by listing only the study number on the CRF. Only the CRF will be used for subsequent scientific evaluation of the study. Data from the lactulose breath test will be transferred to an electronic form.

- 1. Data handling

Subject data will be collected during screening on an anonymized CRF and will be entered in an electronic form. During and at the end of the project period data will be transferred into the electronic form. After the end of data collection the electronic form will be frozen.

- - 1. Documentation and storage

The investigator will create an Investigator Site File and is responsible to keep this Investigator Site File updated and available for review by a study monitor. All paper documents will be stored at the investigator site (Klinik für Gastroenterologie and Hepatologie, UniverstätsSpital Zürich) in room A-West 23. All documents pertaining to the conduct of the study must be kept by the investigator for a period of 10 years.

- 1. Sample storage and further analysis

After finishing this study, fecal and urine samples will be stored in a -80°C freezer at the department of microbiology, ETH Zurich (Hönggerberg). Depending on the outcome of this study additional analysis might be of interest (e.g. genome sequencing of some isolates of the gut microbiota). Additional microbiological, genetic, immunological and biochemical analyses might follow.

1. Suitability of the place of inspection
   1. Team

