**Secondary objectives:**

- Changes in metabolic profiles upon lactulose intake within the gut microbial community (measured in fecal samples) and its impact for the host metabolism (measured in urine samples).
- Inflluence of basic epidemiological parameters (age, gender, country of origin, exercise, smoking) on composition of gut microbiota.
- Influence of microbiota on hydrogen concentration in lactulose breath test
  1. Study procedures, methods outcomes

For this study we will recruit healthy volunteers from ETH Zurich/University of Zurich. Only individuals with training and experience handling liquid nitrogen and -80°C freezers (BL2) will be included in this study. The volunteers will use goggles, gloves and will wear lab coats to snap-freeze the fecal samples. For encoding, cryo-tubes will be labeled with the study number and the day only and the name and personal information will only be known to the physician recruiting the proband for the study. .

The first sample of stool and urine will be collected by the proband one to three days before the lactulose breath test (date will be indicated on the tube). Subsequently, the volunteers will undergo a lactulose breath test or a sham test. Probands will be randomized using a sealed envelope method to receive either 50g lactulose or 50g sucrose in 200 ml water. The study design will be double blinded and neither the study nurse nor the proband will know about group assignment. After ingestion of lactulose/sucrose, hydrogen concentrations in the breath of the individuals will be monitored (baseline level, 30 min, 60 min and 120 min after lactulose/sucrose intake).

Within the next two days, the proband will collect a fecal and urine samples during his or her working hours as described above (date will be indicated on the tube). 14 days after the breath test, a third fecal and a third urine sample will be collected.

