Before the study, there will be one study visit to inform the probands and to obtain informed consent and address basic medical history and gastrointestinal complaints. This is done by one of the MDs in a seminar room at the Institute of Microbiology, ETH Zürich. Specifically, probands will be asked about loss of appetite, nausea, early satiety, sense of abdominal fullness, vomiting, abdominal pain, dysphagia, heartburn, reflux, sweating/ shivering after meals and diarrhea. In addition, probands will be asked about their current medication (proton pump inhibitors, antibiotic therapy, laxative drugs within the last four weeks) previous abdominal surgery, additional chronic diseases, pregnancy, and current or past (≤2 weeks) participation in addition clinical trials (questionnaire Appendix), eating habits (vegetarian, vegan), ethnicity, smokers/non-smokers, the amount of regular physical exercise, stool frequency/consistency (Bristol Stool Scale), weight and height.

The study will be finished within approximately 16 days for each individual. The study includes one examination of approximately 4 hours, the remaining parts of the studies (collection of feces and urine and proper storage of these samples) will be done at the working place of the proband (ETH Hoenggerberg, Zurich).

The anticipated study duration for is from October 2014 to March 2016. Total study duration for each participant is 4 hours maximum (including preparation time) at the study center for the breath test plus collection of fecal samples and urine.

- 1. Method of Randomization and Blinding

To randomly assign our probands to lactulose/sucrose groups, we will apply a sealed envelope technique. Lactulose and sucrose (supermarket) will be filled in tubes labeled with numbers indicated within the envelope. That way, neither the proband nor the study nurse/PI will know the group assignment. Randomization will be ensured using the following program:

<http://www.graphpad.com/quickcalcs/randomize1.cfm>

- 1. Method of encryption

To ensure encryption of samples , cryotubes with fecal and urine samples will be pre-labeled with the study number and the respective date respectively to the breath test. The key for encryption will be stored at University Hospital Zurich. Therefore, only the principal medical investigator, but not the microbiologists will be able to decode the study number and assign this identifier to an individual.

- 1. Unblinding Procedures (Code break)

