Subjects may be discontinued from study treatment and assessments at any time, at the discretion of the Principle Investigators. Specific reasons for discontinuing a subject from this study are:

• Withdrawal of informed consent

• Protocol non-compliance (protocol deviation)

- - 1. Voluntary discontinuation by a subject

Subjects are free to discontinue their participation in the study at any time. Subjects who discontinue from the study should always be asked about the reason(s) for their discontinuation and about the presence of any adverse events. Adverse events should be followed up. Data of these probands will be analyzed. However, data of probands will be anonymized and all contact data and identifying information will be deleted from the subject identification log..

1. Efficacy variables

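### Adverse events in completers are recorded only if volunteered or observed, and no stool form is described for any of the three stool samples: a cheap improvement

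*Protocol*

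**What the plan says.** Protocol 10.2.2 ((S)AE recording) gives two routes by which an event enters the record: "Any (S)AE as reported spontaneously by the subject or observed by the investigator or staff, is recorded on the AE form". Section 5.4.1 goes further for one group: "Subjects who discontinue from the study should always be asked about the reason(s) for their discontinuation and about the presence of any adverse events". No matching instruction is given for volunteers who finish.

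Section 4.2 places the symptom questions ahead of the drink: "there will be one study visit to inform the probands and to obtain informed consent and address basic medical history and gastrointestinal complaints". It then lists them: "Specifically, probands will be asked about loss of appetite, nausea, early satiety, sense of abdominal fullness, vomiting, abdominal pain", followed by further items ending with diarrhea. The same interview covers "stool frequency/consistency (Bristol Stool Scale), weight and height". For the samples themselves, "cryo-tubes will be labeled with the study number and the day only".

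Section 12.2 counts among the source data the "questionnaires filled out by the proband before the examination". Sections 7.2 (Lactulose breath test) and 11.3.2 name diarrhea, bloating and mild abdominal pain as minor adverse events of the test; 11.3.2 also names discomfort. Section 10.2 undertakes to report every adverse event.

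**The concern.** The protocol expects gastrointestinal effects of the drink, but describes no point after it at which a volunteer who completes is asked about them. Mild bloating or a loose stool is the kind of event a volunteer may not think worth mentioning, so the record for completers could be thinner than 10.2 intends.

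The second part concerns interpretation. The primary objective is a change in microbial composition, measured in stool. With no stool form recorded alongside each sample, a reader who sees a shift at 1-2 days cannot tell from the described data whether it came with loose stools. The sample taken before the drink has the same gap, because the Bristol Stool Scale is tied to the earlier consent visit and not to that sample.

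**Working it through.** The protocol states no adverse event rate, so there is no figure to reproduce. The check sets the text side by side and adds simple counts.

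**Who is asked, and when**

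- Before the study (4.2): symptom list and Bristol Stool Scale, once.
- Breath test visit (4.2): hydrogen at baseline, 30, 60 and 120 minutes, within a visit of about 4 hours. Staff can observe here, and 10.2.2 covers that.
- Within the next two days (4.2): one stool and one urine sample, collected, frozen and stored by the volunteer at the workplace. No questions are described.
- Day 14 (4.2): the same, again with no questions described.
- Discontinuation (5.4.1): adverse events are always asked about.
- Nurse's compliance check (6.2): three items, namely substances that alter the gut microbiota, samples, and the breath test. It is a compliance list, so the absence of symptoms is unsurprising, but it also means that it does not fill the gap.

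Section 12 mentions only one hospital visit. Staff observation is therefore realistic mainly during that visit.

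**Who the completers are.** Section 8.4 replaces dropouts until 40 complete sets exist, 20 per group. All 40 volunteers behind those sets fall under the passive rule.

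**Stool samples without a described stool-form record**

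- All samples: 40 volunteers × 3 samples = 120.
- Post-dose samples: 20 per arm × 2 arms × 2 time points = 80.
- Samples for which the text describes a stool-form record: 0 of 120, hence 0 of the 80 post-dose samples.

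**Does the existing list fit the expected effects?** The 4.2 list has 11 entries: loss of appetite, nausea, early satiety, abdominal fullness, vomiting, abdominal pain, dysphagia, heartburn, reflux, sweating or shivering after meals, and diarrhea. Of the three effects named in 7.2, two are on it by name (diarrhea, abdominal pain). Bloating is not; abdominal fullness is the nearest entry. The list can be reused with one item added.

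**The case against.** **The case against is substantial.** Spontaneous reporting is a permitted way of collecting adverse events. None of the objectives in 4.1 concerns safety or tolerability, no comparison of adverse events is planned, and the study gives one dose of a routine diagnostic agent in risk category A (3.4). All of this stands, and it limits the point to an improvement.

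**Unseen forms.** The case report form is meant to hold all relevant participant data (12.2), and 4.2 refers to a questionnaire appendix. Neither is shown, nor is the adverse event form. The source data list in 12.2 is not exhaustive, and the tube label is a coding rule that does not exclude a separate stool record. So 0 of 120 counts what the text describes, not what will be collected. This stands too.

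**Section 10.3** requires the investigator to be told at once of health problems, with no limit to urgent ones. That is a real instruction to report. It still relies on the volunteer to start, and it sits in an insurance clause, so it does not replace asking.

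**Stronger readings that a reader might infer:**

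- *The comparison of lactulose with sucrose is biased.* The documents do not support this. The same rule applies to both randomised groups, and composition is measured whether or not symptoms are recorded.
- *The analysis should adjust for stool form after the drink.* It should not. Diarrhea caused by lactulose is part of the randomised effect, and adjusting would remove some of what is to be estimated.
- *The number of missed events can be estimated.* With an assumed share p of the 20 lactulose volunteers affected and an assumed share r of those who mention it, the number missed is 20 × p × (1 − r). This gives 20 × 0.2 × 0.3 = 1.2 up to 20 × 0.6 × 0.7 = 8.4. Neither p nor r is in the protocol, so the range only restates the assumptions and is not evidence of size.

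**Conclusion.** The point holds as a low-cost improvement. In the protocol text, completers' adverse events are recorded only if they are volunteered or seen by staff, although the protocol itself expects such events. Stool form is described for the pre-study visit and for none of the 120 stool samples. The gain from a change would be fuller recording of expected events and a descriptive aid to reading the composition results. The validity of the randomised comparison is not in question.

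The size of any under-recording is unknown. The conclusion rests on one assumption: that the forms not shown contain no page for symptoms or stool form at the sampling points. If they do, only a cross-reference is missing.

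**What to change.** **In 4.2, add:** *With each of the three stool samples the volunteer records the Bristol Stool Scale. With the 1-2 day and 14 day samples the volunteer also completes the symptom list of this section, with bloating added, covering the time since the drink (1-2 day form) or since the previous form (14 day form). Forms carry the study number only and go to the study nurse when each sample is stored.*

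**In 10.2.2,** insert a third route between the two existing ones: *marked on a post-dose symptom form*.

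Prompt hand-in matters. If the 1-2 day form waited for the last samples, it would reach staff about 12 days late (14 − 2), which would delay grading and follow-up. The stated recall periods ensure that days 3 to 13 are covered. The pre-dose stool record gives the baseline sample its own stool form.

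Use post-dose stool form descriptively only, not as an adjustment covariate. If the case report form or questionnaire already has such a page, 4.2 and 10.2.2 need only refer to it.

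**Cost:** 40 × 3 = 120 Bristol entries and 40 × 2 = 80 symptom lists, built from existing items plus one, at existing sampling points and without an extra visit. The downside is that more minor events will be recorded, each needing severity and relatedness grading under 10.2.2.
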